#### Voice and breathing sounds

We developed speech commands to capture commonly occurring and easily measured speech interactions. The commands are designed to be realistic in a setting outside of a study, meaning their length is similar to an interaction when giving commands to a voice assistant but also fit in the general story and setting of BEDDA. We implemented the voice commands in Breeze. To start and finish Breeze, the participants are visually instructed to say the three simple sentences before and after described above. Besides these voice interactions, we also derive the breathing sounds from Breeze. As the participant follows a guided breathing training each session with Breeze provides a set of inhalation, exhalation, and pause sounds.

#### Audio features

From the different voice commands, we will extract different features reported in related work [16, 22]. We will extract vocal folds features (i.e., source features, e.g., jitter [%], shimmer [%], tremor [Hz]), vocal tract filter features (e.g. F_1_ mean [Hz], F_2_ mean), and prosodic features (i.e., melodic, e.g., F_0_ mean, F_0_ variability, intensity [dB]). We will approach the extraction of acoustic breathing features in a more exploratory way since less related work exists regarding breathing-based biomarkers for depression. For the analysis of breathing sounds, we plan to look at the spectrograms, MFCCs, and GTCCs of the recorded breathing sounds used in previous work [91, 92].

#### Proximal and distal outcomes

Following our conceptual model, we measure proximal and distal outcomes. Proximal outcomes are the symptom changes and physiological data changes (e.g., HRV, physical activity, sleep) due to the daily interactions, while distal outcomes are the symptom severity changes over the course of the intervention. For the investigation of efficacy, we use both proximal outcomes (daily reported symptoms) and distal outcomes (symptom severity changes).

For the daily measurements (i.e., proximal outcomes) before and after interacting with Breeze, we use the Multidimensional Mood State Questionnaire (MDMQ) [88, 89], which has the three dimensions mood, agitation, or anhedonia, and two versions (Version A and B). We will infer one of the dimensions using the two versions (one before and one after interacting with the main component Breeze) at each daily interaction. For example, on a given day, the randomly chosen dimension is mood. Then, another draw determines that the questions from version A should be used to measure mood before Breeze. In turn, the questions from Version B are used to measure mood after Breeze. To ensure equal distribution of the daily drawn dimensions and versions, we use a block design consisting of the six question sets (Mood_A_, Mood_B_, Agitation_A_, Agitation_B_, Anhedonia_A_, Anhedonia_B_) and draw from this set until each was drawn once before starting with a new block for the following six days.

Our primary distal outcome is depression symptom severity, which we measure using the PHQ-9. The PHQ-9 is a subset of the Patient Health Questionnaire [44] and focuses on major depressive disorder. It is used to measure the severity of symptoms of depression in general medical and mental health settings [44]. Our secondary distal outcomes are anxiety (measured using the GAD-7) and stress (measured using the TICS). The General Anxiety Disorder-7 Questionnaire (GAD-7) is a clinically validated instrument to screen for symptom severity for the four most common anxiety disorders (Generalized Anxiety Disorder, Panic Disorder, Social Phobia, and Post Traumatic Stress Disorder) [87]. The Trier Inventory of Chronic Stress Short Version (TICS) measures all nine domains of the systemic-requirement-resource model of health [93] of an individual. It is the short version developed from the original long version of the Trier Inventory for Chronic Stress [94]. All distal outcomes are measured at T_0_, T_1_, T_2_, and T_3_ to determine symptom severity and to assess the efficacy BEDDA.

#### Other measurements

To measure the therapeutic alliance between BEDDA and the participants, we will use the Working-Alliance Inventory (WAI) [64]. We will use further qualitative open answer questions regarding BEDDA and Breeze at T_3_. Furthermore, we will ask where the participant is conducting the breathing training before starting Breeze and how accurately the breathing detection was on that day after Breeze (daily). During the interaction with Breeze, we also collect additional sensor data from the following sensors if they are present on the device: accelerometer, gyroscope, magnetometer, light sensor, ambient temperature sensor, humidity sensor, pressure sensor, step counter (since app start), and proximity sensor. The other sensors provide more information about the surroundings during the breathing training and help determine whether the person is doing the exercise correctly (e.g., steps taken during the training).

#### Smartwatches

Participants in the smartwatch groups (intervention and waitlist) will receive a smartwatch (Garmin Vívosmart 4 Smartwatch, Garmin International Inc., [name]) at the start of the study. The measurements recorded by the smartwatch are heart-rate and heart-rate variability (via inter-beat-intervals), oxygen saturation, respiration rate, motion-based activity (3-axis accelerometer), stress level, sleep, skin temperature, and steps.

### Estimation of sample size

Sample size calculations for machine learning approaches, such as for objectives one and two, are less rigorously described compared to sample size estimations for investigation of efficacy. Therefore, we calculated the sample size needed for objective three and used this number of participants to estimate the expected correlation between features and outcomes for objectives one and two.

The third objective of our study is to investigate the efficacy of BEDDA. We operationalized this with three assessment times (at the start of the intervention, after 15 interactions, and after 30 interactions) in two groups (intervention and waitlist control). Assuming a small effect (Cohen’s d = 0.225), a power of 0.8, and an alpha level of.05, we calculated that we need at least 194 to detect an existing effect of BEDDA compared to control. Regarding our first and second objectives, we calculated that when 194 participants provide data, assuming a 0.05 alpha level and a power of 0.8, a Pearson moment correlation coefficient of 0.23 would be necessary for a significant result. Low et al. [22] reported a median number of participants for studies investigating voice changes in depression of 123 (with a range from 11 to 1688). With the estimated 194, we are above the mean but in a reasonable range.

Related work collecting data for the development of DBMs has reported a mean adherence rate of 86.6% [40]. Due to the extended assessment period, we assume a greater attrition rate. However, we also consider specific elements of our study (monetary incentives, storytelling, and gamification) that may lead to increased adherence. Considering these factors, we expect a dropout rate of approximately 20%, slightly greater than the dropout rate reported in related work [40]. Assuming this dropout rate, we aim to initially enroll 220 participants.

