### Study design

Figure 8 shows the experimental design of the study. The study will run for 60 days, and participants will be randomly (using an algorithm on the recruitment website) allocated to one of four groups we listed in Table 1: intervention with smartwatch (IG_sw_), intervention without smartwatch (IG_nsw_), waitlist with smartwatch (WG_sw_), waitlist without smartwatch (WG_nsw_). The intervention part of the study will run for 30–45 days, depending on how many days the participant needs to finish the required 30 once-per-day guided interactions (described below). Participants allocated to the intervention group (IG_sw_ and IG_nsw_) will start the experiment first. In their first interaction (T_1_), they will receive the study information, give written informed consent via the app (type of content approved by the ethics committee), complete the initial assessment, receive a tutorial on how to use the app, and complete a training with Breeze for the first time. Participants allocated to the waitlist group (WG_sw_ and WG_nsw_) will complete the baseline assessment (T_0_) but will not yet start using the app for another 30 days. In these first 30 days, participants in the intervention group will interact daily with BEDDA. This interaction includes dialogues with the conversational agent, answering questions before and after Breeze, and conducting breathing training with Breeze. Each day, they can also choose whether they want to receive daily wisdom matching the symptom of the day. Additionally, the conversational agent moves the story further each day, and the app uses gamification elements to illustrate progress. On day 15 of the intervention, participants allocated to the intervention group will respond to the half-time assessment questions and on day 30, participants in the intervention group will respond to the final assessment.

**Table 1 Tab1:** Groups included in the study

Group	Treatment	Smartwatch	Planned N
IG_sw_	Intervention	Yes	25
IG_nsw_	Intervention	No	75
WG_sw_	Waitlist	Yes	25
WG_nsw_	Waitlist	No	75

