For the second objective, we will proceed in a comparable matter. However, the dependent variables in these models are the symptom severity assessed by the PHQ-9 (depression), GAD-7 (anxiety), and TICS (stress). The independent variables remain the same (voice, breathing, physiological) with a potential extension of using the developed symptom markers from the second objective as additional independent variables. Due to only three assessment times (T_1_, T_2_, T_3_) resulting in three measurements for each participant, we will not be able to develop intra-subject models but will focus on generalizable models for the entire population. Similar to the second objective, we will also infer whether voice and breathing are complementary or alternative markers using a triangulation approach [95].

For the third objective, the estimation of efficacy, we differentiate between proximal and distal outcomes. We based this analysis on a the micro-randomized trial as introduced by Klasnja et al. [59]. However, we have the limitation that the outcomes measured are randomized and not the component. Therefore, we will use Generalized Estimating Equations (GEE; e.g., [96, 97]) to analyze the changes in proximal outcomes. Distal outcomes are the symptom severity changes as determined by the PHQ-9 (depression), GAD-7 (anxiety), and TICS (stress). As stated above in the section regarding sample size estimation, the primary distal outcome is symptom severity of depression. Due to this focus, our first analysis will be a two-way mixed ANOVA (2 groups $$\times$$ 3 measurement times). To investigate post-hoc, whether other factors such as belonging to the smartwatch group, age, and gender have an impact on a potential reduction of severity, we aim to use mixed effect linear regression (hierarchical groups such as intervention and smartwatch vs. no-smartwatch groups). In later analyses, we will investigate intercorrelations between the different dependent variables (PHQ-9, GAD-7, TICS) using a two-way mixed MANOVA (2 groups $$\times$$ 3 measurement times $$\times$$ 3 outcomes). We may compute additional MANOVAs comparing theoretically or empirically connected physiological outcomes to the three distal outcomes if physiological data allow such analyses.

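### The printed inputs (Cohen's d = 0.225, power 0.8, alpha 0.05) do not give 194 participants; 80% power for that effect needs an unstated within-person correlation of about 0.83 or more

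*Protocol article*

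**What the plan says.** Protocol article, Estimation of sample size, on the efficacy objective. The design behind the calculation is given as: "We operationalized this with three assessment times (at the start of the intervention, after 15 interactions, and after 30 interactions) in two groups". Those groups are the immediate-start arm and the waitlist arm. The power claim reads: "a power of 0.8, and an alpha level of.05, we calculated that we need at least 194 to detect an existing effect of BEDDA". The effect size entered in that claim is 0.225, labelled as Cohen's d and called small. The section then expects about 20% dropout and plans to enrol 220. Table 1 under Study design gives equal allocation between intervention and waitlist.

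Protocol article, Planned analysis, on PHQ-9 as the primary distal outcome: "our first analysis will be a two-way mixed ANOVA (2 groups" by three measurement times).

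The article does not state the tested term, the within-person correlation, the sidedness of the test or the software.

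**The concern.** The article prints both its inputs and its result, so the calculation can be checked. With 97 per arm, 80% power for a standardised difference of 0.225 would be surprising unless repeated measurement removes most of the variance.

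This is the only sample-size argument for efficacy, and the biomarker objectives reuse its N. If the claim is wrong, readers will believe that the trial can detect a small effect when it may well not. A null PHQ-9 result could then be taken as evidence against a benefit of 0.225 SD that the trial had limited power to show.

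**Working it through.** **Inputs from the article:** d = 0.225, power 0.80, alpha 0.05 (taken as two-sided, or as an F test), N = 194 in total, 1:1 allocation (97 per arm), 2 groups x 3 times.

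**Assumed, because not stated:** within-person correlation rho, equal across visits, at 0.5, 0.7 and 0.8; no group difference at the start; equal SDs.

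**1. Trying to reproduce 194 from d = 0.225.**
- *Two-group comparison at the end.* The normal approximation gives n per arm = 2(1.960 + 0.842)²/0.225² = 310.1, so 311 per arm (622 in total). The noncentral t gives power 0.79995 at 311 and 0.8012 at 312 per arm, so 624 in total. At 97 per arm, power is 0.344. One-sided, the need is about 490, with 47% power at 194.
- *Group main effect over three visits*, with f = d/2 = 0.1125: N runs from 209 (rho = 0) to 540 (rho = 0.8).
- *Group-by-time interaction*, entering f = 0.1125 with lambda = 3Nf²/(1 − rho): N = 129 at rho = 0.5. At N = 194, lambda = 3 x 194 x 0.01266/(1 − rho) = 7.37/(1 − rho). Power of 80% needs lambda = 9.71 on 2 and 384 df, which gives rho = 0.24.

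Only the last route reaches 194, at a correlation that is not stated. That f does not describe an end difference of 0.225. With a zero starting difference it implies 0.1125 x √24 = 0.55 SD (linear growth) or 0.1125 x √18 = 0.48 SD (full difference from half-time).

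**2. What does return 194.** Take f = 0.225 with 2 numerator df.

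| Denominator df | lambda | Power at 193 | Power at 194 |
|---|---|---|---|
| N − 6 | Nf² | 0.7991 | 0.8013 |
| N − 3 | Nf² | 0.7992 | 0.8014 |
| 2(N − 2) | (N − 2)f² | 0.7982 | 0.8004 |

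All three give 194 as the smallest N, with no free parameter.

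**3. Power of the planned group-by-time test at d = 0.225, N = 194.** Let D1, D2, D3 be the group differences at the three visits. Then f² is the mean of ((Dt − mean D)/2)², and lambda = 3Nf²/(1 − rho).
- Linear growth (0, d/2, d): f² = d²/24, so lambda = Nd²/(8(1 − rho)).
- Step from half-time (0, d, d): f² = d²/18, so lambda = Nd²/(6(1 − rho)).

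With Nd² = 194 x 0.050625 = 9.821:

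| rho | lambda, linear | Power | lambda, step | Power |
|---|---|---|---|---|
| 0.5 | 2.46 | 27% | 3.27 | 35% |
| 0.7 | 4.09 | 42% | 5.46 | 54% |
| 0.8 | 6.14 | 59% | 8.18 | 72% |

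Setting lambda = 9.71 gives the rho needed for 80%: 1 − 9.821/(8 x 9.71) = 0.87 (linear) and 1 − 9.821/(6 x 9.71) = 0.83 (step).

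**4. End difference detectable with 80% power.** Solving lambda = 9.71 for d gives √(9.71 x 8(1 − rho)/N) for linear growth, with 6 in place of 8 for the step. The 176 is 220 x 0.8; multiply by √(194/176) = 1.05.

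| rho | 194, linear | 194, step | 176, linear | 176, step |
|---|---|---|---|---|
| 0.5 | 0.45 | 0.39 | 0.47 | 0.41 |
| 0.7 | 0.35 | 0.30 | 0.36 | 0.32 |
| 0.8 | 0.28 | 0.25 | 0.30 | 0.26 |

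**The case against.** The strongest reply is that a condensed article need not print a correlation, that repeated measures can add much precision, and that with a high enough correlation 194 does deliver 80% at d = 0.225. The first two parts stand: the missing correlation is not itself the error. The third is true only from about 0.83 (step) or 0.87 (linear), and the article offers nothing to support such values.

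Three stronger readings are tempting, and the document does not support them.

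- *The three visits were treated as different people.* The df of N − 6 fits that story, but the N − 3 and 2(N − 2) versions also return 194, and both are repeated-measures forms for this design. The match points to f = 0.225 with 2 numerator df and no further.
- *The intended effect was d = 0.45.* That uses f = d/2, the conversion for two independent groups. If f = 0.225 already absorbed the correlation, the end difference varies with rho and the time pattern, and the 194 columns in step 4 apply. The route with f = 0.1125 and rho near 0.24 also remains open.
- *The true power is some fixed low figure.* It depends on rho and on the trajectory, and neither is documented. A baseline-adjusted end comparison would give other figures, but it is not the analysis planned here.

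**Conclusion.** Wrong as written. On the printed inputs, 194 participants do not give 80% power for d = 0.225. The shortfall is large for a plain end comparison (34% power; about 624 needed). For the planned interaction test, power is 27% to 72% over correlations of 0.5 to 0.8 and the two time patterns. It reaches 80% only with a correlation of about 0.83 to 0.87.

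That the inputs and the result disagree is firm unless such a correlation was assumed. That f was labelled d is the likeliest explanation but unproven. The power figures rest on equal correlations across visits, equal SDs, no difference at the start, and complete data on all 194. A reader might also infer that the trial must recruit more. That does not follow, because the article does not say that 0.225 SD is the smallest difference worth detecting.

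**What to change.** In Estimation of sample size:

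1. Correct the effect-size metric, saying whether 0.225 is Cohen's f or d and, if f, how it was defined.
2. Name the tested term (group-by-time in the 2 x 3 mixed ANOVA) and the assumed within-person correlation.
3. Recompute for that test.
4. Replace the claim about a small effect with the detectable end difference and its assumptions. For example: at 194 evaluable, 80% power for an end difference of about 0.45, 0.35 or 0.28 SD (linear growth), or 0.39, 0.30 or 0.25 SD (full difference from half-time), at correlations of 0.5, 0.7 and 0.8. Give the slightly larger values for the 176 expected after 20% dropout from 220.

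The cost is one recalculation and a change of wording. Recruitment is unaffected; the stated detectable effect becomes less favourable.

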## Planned analysis

We plan different analyses for the different research objectives, which we will describe in this section. This description cannot be holistic for the machine learning analyses (first and second objective), as we plan to explore different machine learning algorithms. For an initial overview, we aim to provide a distribution of the daily measured proximal symptoms and the measured distal severity. The choice of algorithms will depend on the observed performance of the resulting models. Regardless of the analysis, we will split the data into a training and a hold-out testing set. Using the training set, we will train and evaluate machine learning algorithms using cross-validation. This will allow us to compare machine learning algorithms, including different feature extraction pipelines, and determine which performs best. In a final step, we will use the hold-out test set to verify the cross-validation results by evaluating the resulting models on completely unseen data.

For the first objective, we plan to investigate different supervised regression models to predict mood, agitation, and anhedonia. We aim to use the following data sources: self-reported mood, agitation, and anhedonia (MDMQ), voice sounds, breathing sounds, reaction time, and physiological smartwatch data. Due to the availability of both features (voice, breathing, and physiological features) and labels (self-reported mood, agitation, and anhedonia), we will focus on supervised machine learning models. We aim to try different machine learning algorithms, such as but not limited to multivariate linear regression models, random forest, and multilayer perceptron models. We will also explore explained variance by the voice and breathing features in self-reported and physiological data using a triangulation approach [95] to determine whether DBMS can be used as an alternative or complementary assessment for symptoms of depression.

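### The planning correlation of 0.23 for objectives one and two does not follow from its stated inputs: 194 participants, alpha 0.05 and power 0.8 give a detectable r of 0.20

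*Protocol article*

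**What the plan says.** The section on estimation of sample size in the protocol article calculates the number of participants for objective three (efficacy) and arrives at 194. It says that the team then "used this number of participants to estimate the expected correlation between features and outcomes for objectives one and two". The calculation is conditional on full data ("when 194 participants provide data") and names its error rates: "assuming a 0.05 alpha level and a power of 0.8". Its result is that "a Pearson moment correlation coefficient of 0.23 would be necessary for a significant result". Sidedness is not stated, and no adjustment for several outcomes is mentioned.

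The planned analysis section describes how the models for objectives one and two will be built and checked: "Regardless of the analysis, we will split the data into a training and a hold-out testing set". Algorithms are compared by cross-validation inside the training part, and the hold-out part serves as a final check. Neither the share held out nor the unit of the split (person or session) is given. For objective two the section adds that "we will not be able to develop intra-subject models but will focus on generalizable models for the entire population".

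**The concern.** The sentence gives every input except sidedness, so the result can be checked directly, and it does not reproduce. It also merges two quantities. One is the true correlation that a study of this size would detect with 80% power. The other is the smallest observed correlation that would reach significance. The value 0.23 is neither.

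This is the only quantitative statement about what the sample can show for two of the three objectives. A reader who relies on it would misjudge which feature–outcome correlations are within reach. The figure also uses all participants, so a reader could carry it over to the hold-out check, which rests on fewer people.

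**Working it through.** **Inputs, all from the section on estimation of sample size:** n = 194; alpha = 0.05; power = 0.80; stated r = 0.23. Two-sided testing is assumed because sidedness is not stated; the one-sided value is also shown.

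**Step 1. Attempt to reproduce 0.23.** The detectable correlation by Fisher z is r = tanh((z_alpha + z_power)/√(n − 3)).

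- Two-sided: (1.960 + 0.8416)/√191 = 2.8016/13.820 = 0.2027, and tanh(0.2027) = **0.200**.
- One-sided: (1.645 + 0.8416)/13.820 = 0.1799, and tanh(0.1799) = **0.178**.

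Other methods agree with the two-sided result. A t-based critical value with bias-corrected Fisher z gives 0.1995, and a noncentral-t calculation gives 0.198. In a simulation of 40,000 data sets the power at r = 0.20 was 80.1%.

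**Step 2. What 0.23 would mean at n = 194.**

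- Power at r = 0.23: atanh(0.23) × √191 − 1.960 = 0.2342 × 13.820 − 1.960 = 1.277, which is 89.9% power (also 89.9% in simulation).
- Participants needed for 80% power at r = 0.23: (2.8016/0.2342)² + 3 ≈ 146.1, so about 146 (147 rounded up).

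**Step 3. Is 0.23 the significance threshold?** The critical observed r is t/√(df + t²) with df = 192 and t = 1.972: 1.972/√(192 + 3.890) = **0.141** two-sided (0.118 one-sided). It is not 0.23.

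**Step 4. Which changed inputs give 0.23?**

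| Changed input | Resulting r |
|---|---|
| Power 0.90, two-sided, n = 194 | 0.2303 |
| Alpha 0.05/3, power 0.80, two-sided, n = 194 | 0.2299 |
| One-sided alpha 0.05, power 0.95, n = 194 | 0.2336 |
| n = 146, power 0.80, two-sided | 0.2301 |

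Each departs from at least one stated input, and the article mentions none of them.

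**Step 5. Scale of the hold-out check (illustration only).** The article gives no split share. Assume that 20% to 30% of 194 participants are held out, that is 39 to 58 people with one value each. The same formula then gives a detectable r of 0.44 to 0.36, and power at r = 0.23 of about 29% to 41%. This shows only that the planning figure does not transfer to a smaller subset. It is not an estimate of how the hold-out check will perform.

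**The case against.** The strongest objection is that the error harms nothing. The number of participants was fixed by objective three, and the correlation was derived from it afterwards. The stated value is also larger than the correct one, so the sample is more sensitive than the text claims. This stands, and it limits the weight of the point. A reader might infer that the study is too small for objectives one and two; this error does not show that.

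A second objection is that the figure may be right and an input misreported. With three outcomes per objective, an alpha of 0.05/3 is conceivable, as is 90% power. This also stands: the text cannot show which number is wrong, only that figure and inputs disagree.

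Two stronger readings are tempting and are not supported:

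- **That the article overstates what the hold-out check can show.** The 0.23 is described as a correlation between features and outcomes, not between predicted and observed values in a test set. No significance test on the hold-out set is stated, models are compared by cross-validation in the training set, and repeated sessions per person may add information. The figures in Step 5 rest on an assumed split.
- **That the same person's sessions will sit in both training and test sets and inflate performance.** The article does not state the unit of the split. It calls the test data wholly unseen, and for objective two it seeks models for the whole population. In a condensed article, silence on this detail is not evidence of leakage. For objective one, within-person models are not ruled out, and there a within-person split could be legitimate.

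**Conclusion.** The stated correlation is wrong as written. With 194 participants, alpha 0.05 and power 0.8, the detectable correlation is 0.20 two-sided and 0.18 one-sided, not 0.23. The reference to significance is also wrong, since that threshold is 0.14. The arithmetic assumes a simple Pearson correlation with one pair of values per participant, which is how the sentence presents it.

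The error is conservative on the full sample and leaves the sample size unchanged, so it is a reporting correction and not a design flaw. The figure applies to feature–outcome correlations on all participants and does not give the precision of the hold-out evaluation. The article does not claim that it does, but saying so would prevent the misreading. The unit of the split is a point to clarify, not a proven fault.

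**What to change.** In the section on estimation of sample size:

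1. Restate the result as r = 0.20 for n = 194, two-sided alpha 0.05 and 80% power. If 0.23 was obtained with another power or alpha (for example 90% power or alpha 0.05/3), state those inputs instead.
2. Replace the wording about what a significant result requires with a statement that the correlation is detectable with the stated power.
3. Add that the figure is a feature–outcome correlation on all participants and does not describe the precision of the smaller hold-out check.

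As an optional clarification in the planned analysis section, say that the split for the population-level models is made by participant, leaving room for any within-person models under objective one.

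The cost is a few sentences. No sample size, data collection or stated analysis changes.

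### Enrolling 220 with the stated 20% dropout leaves 176 participants, not the required 194, and Table 1 plans a different total of 200

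*Protocol article*

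**What the plan says.** The section on estimation of sample size bases the number on objective 3, with "three assessment times (at the start of the intervention, after 15 interactions, and after 30 interactions) in two groups (intervention and waitlist control". Its inputs are "Assuming a small effect (Cohen’s d = 0.225), a power of 0.8" and "an alpha level of.05", and its result is that "we calculated that we need at least 194 to detect an existing effect of BEDDA compared to control". The same number is carried to objectives 1 and 2: "we calculated that when 194 participants provide data", a Pearson correlation of 0.23 is given as the size needed at alpha 0.05 and power 0.8.

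The section then turns to attrition. It cites a mean adherence of 86.6% from related work, says it assumes greater attrition than that, and states "we expect a dropout rate of approximately 20%, slightly greater than the dropout rate reported in related work [40". From this it derives the recruitment target: "Assuming this dropout rate, we aim to initially enroll 220 participants".

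The study design section says that participants are randomly "allocated to one of four groups we listed in Table 1". The planned-N column of that table reads 25, 75, 25 and 75.

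**The concern.** The enrolment target is presented as the result of inflating 194 for 20% dropout, but it is too small to be that. If recruitment stops at 220 and dropout is as expected, the trial ends below its own declared minimum for the efficacy comparison on the PHQ-9. A reader of a null result would take the stated 80% power at face value. The article also gives two planned totals, 220 in the text and 200 in the table, so it is unclear when recruitment is complete.

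**Working it through.** **Inputs.** From the sample size section: required number 194, dropout about 20%, adherence in related work 86.6%, enrolment 220, correlation 0.23, alpha 0.05, power 0.8. From Table 1: 25, 75, 25, 75.

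**1. Attempt to reproduce 220.**
- Standard inflation, N/(1 − dropout): 194/0.80 = 242.5, so 243 (244 for equal arms).
- The common mistaken inflation, N × (1 + dropout): 194 × 1.20 = 232.8, so 233.
- With the 13.4% loss implied by 86.6% adherence: 194/0.866 = 224.02, so 225. The mistaken form gives 194 × 1.134 = 220.0.

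Neither route at 20% gives 220. The only match found is the mistaken formula applied to 13.4%. That may be where 220 came from, but the article does not say so, and 13.4% is not the rate it says it assumes.

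**2. What 220 delivers.**
- 220 × 0.80 = 176. Shortfall 194 − 176 = 18, and 18/194 = 9.3%.
- Largest dropout at which 220 still leaves 194: 1 − 194/220 = 11.8%.
- Sensitivity to the word *approximately*: 15% dropout leaves 220 × 0.85 = 187, and 13.4% leaves 220 × 0.866 = 190.5. Both miss 194.

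**3. Table 1.**
- 25 + 75 + 25 + 75 = 200, against 220 in the text.
- If these are numbers allocated before dropout: 200 × 0.80 = 160. Shortfall 194 − 160 = 34, and 34/194 = 17.5%. On that reading 194 survives only if dropout is at most 1 − 194/200 = 3.0%.

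**4. Power for objective 3.** This needs a model that returns 194, and the article does not fully specify one. A plain two-arm comparison of means at d = 0.225 needs 311 per arm. A repeated-measures ANOVA with f = d/2 = 0.1125 gives totals from 54 to 256 for the interaction, as the assumed correlation between measurements runs from 0.8 down to 0. Among the models tried, the one that returned exactly 194 was a fixed-effects F test with f = 0.225 and 2 numerator degrees of freedom. With noncentrality f² × N, its power is:

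| Participants with data | Power |
|---|---|
| 194 | 0.80 |
| 176 | 0.76 |
| 160 | 0.71 |

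This model is my inference. For scale only, an unadjusted two-arm t-test (two-sided 0.05, 80% power, equal arms) has a detectable standardised difference of 0.404 at 194, 0.425 at 176 and 0.446 at 160. That is not the planned analysis either.

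**5. Objectives 1 and 2.** By Fisher's z, two-sided alpha 0.05 (sidedness is not stated, so this is assumed), power ≈ Φ(atanh(r) × √(N − 3) − 1.96), with atanh(0.23) = 0.234:
- N = 176: 0.234 × √173 − 1.96 = 1.12, power about 87%.
- N = 160: 0.234 × √157 − 1.96 = 0.97, power about 84%.
- r = 0.23 reaches 80% power at ((1.96 + 0.84)/0.234)² + 3, about 147 participants.

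The stated correlation therefore remains detectable with more than 80% power at both reduced numbers.

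**The case against.** The best defence is that the dropout figure is approximate and the loss modest. The first part fails, because dropout would have to be 11.8% or less. That is below even the 13.4% implied by the adherence the article cites, which it says it expects to exceed. (One minus mean adherence is only a rough stand-in for dropout, but the article makes that comparison itself.) The second part stands: on the inferred model, enrolling 220 costs about 4 percentage points of power, and the error biases no estimate or analysis.

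Three stronger readings are tempting and are not supported.

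- A reader might infer that the shortfall also undermines the detectable correlation for objectives 1 and 2. It does not: 0.23 keeps about 87% power at 176 and 84% at 160. Only the premise that 194 will provide data fails.
- A reader might take 76% and 71% as the sponsor's own power at the reduced numbers. The article labels its effect as Cohen's d and gives neither an f nor degrees of freedom, and its planned analysis is a two-way mixed ANOVA. The figures hold only if the inferred model is what was used.
- A reader might treat 160 as the planned number of completers. The wording on allocation supports reading Table 1 as numbers allocated, but does not settle it. The table could instead be a rounded target for analysed participants, since 200 lies just above 194. Even then, 220 enrolled at 20% dropout gives 176, so neither 194 nor 200 would be reached.

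**Conclusion.** Wrong as written. On the article's own inputs, 220 enrolled with 20% dropout gives 176, which is 18 below the stated minimum of 194. This takes 194 as the stated need; whether 194 follows from the stated effect size is a separate question. The mismatch between 200 and 220 is also certain, while the figure of 160 depends on what Table 1 counts.

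The consequence is confined to objective 3: the stated 80% power is not delivered at the expected number of completers. The size of the loss is conditional on the inferred model, at about 4 points for 176 and 9 points for 160. The power stated for objectives 1 and 2 is not lost.

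**What to change.** 1. Give one enrolment target, the same in the sample size section and in Table 1, and say whether Table 1 counts participants allocated or analysed.
2. Then do one of two things. Either state the evaluable number expected after 20% dropout (176 if 220 are enrolled) and restate the objective 3 power or detectable effect for it, naming the model used. Or state that 220 preserves 194 only if dropout does not exceed 11.8%.
3. For objectives 1 and 2, replace the reference to 194 providing data with the expected number. The correlation of 0.23 can stay.

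Enrolling 243 (244 for equal arms) would also resolve the point but is not needed to correct the statement. Items 1 to 3 cost a few sentences and a table edit; the only price is a slightly less favourable power statement for objective 3.
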